## Abstract

**Background:**

Hospitalization in older adults is characterized by physical inactivity and a risk of losing function and independence. Systematic strength training can improve muscle strength and functional performance in older adults. Few studies have examined the effect of a program initiated during hospitalization and continued after discharge. We conducted a feasibility study prior to this trial and found a progression model for loaded sit-to-stands feasible in older medical patients. This study aims to determine whether a simple supervised strength training program for the lower extremities (based on the model), combined with post-training protein supplementation initiated during hospitalization and continued at home for 4 weeks, is superior to usual care on change in mobility 4 weeks after discharge in older medical patients.

**Methods:**

Eighty older medical patients (65 years or older) acutely admitted from their own homes will be included in this randomized, controlled, parallel-group, investigator-blinded, superiority trial. After baseline assessments patients will be randomized to (1) intervention: progressive strength training during hospitalization and after discharge (home-based), or (2) control: usual care. Shortly after discharge, 4 weeks after discharge (primary end point) and 6 months after discharge patients will be assessed in their own homes. The intervention encompasses strength training consisting of two lower extremity exercises (sit-to-stand and heel raise) daily during hospitalization and three times per week for 4 weeks after discharge. Both exercises follow pre-defined models for progression and will be performed for three sets of 8–12 repetitions maximum in each training session. Thereafter, the patient will be asked to consume a protein supplement given orally containing 18 g milk-based protein. The primary outcome will be change in the de Morton Mobility Index score from baseline to 4 weeks after discharge. Secondary outcomes will be 24-h mobility level, isometric knee extension strength, the 30-sec sit-to-stand test, habitual gait speed, hand-grip strength, and Activities of Daily Living.

**Discussion:**

We chose to investigate the effect of a minimal time-consuming treatment approach, i.e. two well-performed strength training exercises combined with protein supplementation, to facilitate implementation in a busy clinical care setting, given a positive trial outcome.

**Trial registration:**

ClinicalTrials.gov: NCT01964482.

## Background

### Background and rationale

Ageing is associated with a decline in muscle strength and functional performance, which is why older adults (aged 65 years or older) do not possess the same reserve capacity as younger adults [1–5]. In general, older hospitalized adults display poor muscle strength and functional performance indicative of poor mobility [6, 7] and are at risk of becoming dependent after acute illness and hospitalization [8–10]. Moreover, hospitalization is associated with a subsequent loss of muscle strength [11], putting hospitalized older adults at a higher risk of losing independence as a consequence of their hospitalization.

During hospitalization, older adults spend most of their time being physically inactive and lying in bed [12–16]. This can lead to a decline in observed and self-reported ability to perform Activities of Daily Living (ADL) at discharge and at 1 month follow-up [14, 17], inducing a risk of dependency [18], and increasing the risk of institutionalization and of death [14]. Older adults are more sensitive to bed rest inactivity compared to younger adults [19–22], and have an impaired ability to fully recover [20, 21]. In healthy older adults, restricted activity and bed rest are associated with reduced protein synthesis and reduced muscle mass and strength [21, 23, 24], and new disabilities in ADL [25, 26]. Similarly, a study by Boyd et al. [9] has shown that new disabilities in ADL are experienced by one third of older medical patients from hospital admission to discharge, and only 30 % of these return to their preadmission level within the first year after discharge [9]. Self-reported decline is seen even after short hospital stays [27]. Thus, reducing physical inactivity during hospitalization and maintaining independency, is considered the most important health outcome by many older adults [28]. Regaining function within the first month after discharge seems especially important as 1-month status is indicative of functional status 1 year after discharge [9].

Systematic strength training can improve muscle strength and functional performance in healthy older adults [29–32], and this has also been reported in patients with chronic diseases [33]. Both strength training initiated during hospitalization in geriatric patients [34], as well as post-discharge training [35, 36] and training of functionally impaired community-dwelling older adults [37], have shown positive effects on strength and functional performance. Most exercise programs for older hospitalized [36, 38–40] or community-dwelling [36, 37, 41–43] adults cover a range of exercises, including upper body and lower body strength training, balance exercises, walking exercises and stretching exercises, but few have examined the effect of a program initiated during hospitalization and continued after discharge [36, 40, 44]. These studies, however, have experienced problems with compliance [36, 40, 44]. A recent systematic review suggests that “the recovery of patients could further benefit from a community-based or an in-home intervention program which build on in-hospital programs” [45]. In addition, acutely hospitalized older adults express the opinion that initiating exercise in the hospital or shortly after discharge is a good idea [44, 46]. Further, supervision can benefit adherence to training [45, 47], and participation is more likely if recommended by a physiotherapist [48]. This emphasizes the importance of supervision by trained staff both in the hospital and in the home setting [40, 44, 49].

Regarding the content of an exercise program, recent reviews suggest that information is lacking about the appropriate dose of strength training in different settings for older adults as well as detailed descriptions of exercises and dosage [29, 50, 51], although it seems that higher intensities are superior to lower intensities [50, 52].

As the lower extremities are especially sensitive to bed rest [23, 53] and lower extremity strength is associated with functional performance (e.g. mobility and the ability to perform ADL) [54–57], it seems reasonable to focus on counteracting loss of strength and functional performance in the lower extremities. Moreover, combining strength training with protein supplementation may be even more beneficial as it may stimulate muscle protein synthesis and thus increase the exercise response on muscle mass and strength as seen in healthy older adults [58–60].

Therefore, the aim of this study is to determine in a randomized, investigator-blinded controlled trial whether a simple, low-technology, supervised strength training program for the lower extremities, combined with post-training protein supplementation initiated during hospitalization and continued at home for 4 weeks after discharge, is superior to usual care on change in mobility 4 weeks after discharge in older medical patients.

## Methods

### Study design

The study, which is called the Cross-Continuum Progressive Strength Training in Older Medical Patients – Copenhagen (STAND-Cph) trial, is a randomized, controlled, parallel-group (two groups), investigator-blinded, superiority trial being conducted in the Copenhagen area, Denmark. The trial investigates the effect of a simple, low-technology, supervised strength training program commenced during hospitalization and continued for 4 weeks after discharge (ClinicalTrials.gov-identifier: NCT01964482). The study is conducted as a full-scale trial following a feasibility study in which we found a progression model for loaded sit-to-stands feasible when used as a simple strength training exercise in older medical patients [61]. Participants will be randomized to either progressive strength training or usual care, and the primary end point will be 4 weeks after discharge (end of exercise period). In addition, the participants will be followed up after 6 months. Table 1 provides an overview of the trial characteristics.

**Table 1 Tab1:** Trial registration data

Data category	Information
Primary registry and trial identification number	ClinicalTrials.gov: NCT01964482
Data of registration in primary registry	14 October 2013
Secondary identifying numbers	The Ethics Committee of the Capital Region of Denmark: H-2-2012-115
	The Danish Data Protection Agency: 2007-58-0015
Source(s) of monetary or material support	Danish Regions/The Danish Health Confederation, The Lundbeck Foundation (UCSF) (grant numbers FP 07/2012, FP 48/2012 and FP 61/2013), the Research Foundation of Hvidovre Hospital, the Capital Region of Copenhagen, and The Danish Foundation for Research in Physiotherapy
Primary sponsor	Danish Regions/The Danish Health Confederation
Secondary sponsor(s)	The Lundbeck Foundation (UCSF), the Research Foundation of Hvidovre Hospital, the Capital Region of Copenhagen, and The Danish Foundation for Research in Physiotherapy
Contact for public queries	[name], TB ([contact])
Contact for scientific queries	[name], TB. Clinical Research Centre, Hvidovre Hospital, University of Copenhagen, Denmark
Public title	In-hospital and post-discharge training of older medical patients
Scientific title	Supervised progressive cross-continuum strength training compared with usual care in older medical patients: study protocol for a randomized controlled trial (the STAND-Cph trial)
Country of recruitment	Denmark
Health condition(s) or problem(s) studied	Progressive strength training in older medical patients
Intervention(s)	Intervention: strength training daily during hospitalization and 3 times per week for 4 weeks after discharge
	Control: usual care
Key inclusion and exclusion criteria	Inclusion criteria: age ≥65 years; acutely admitted from own home to the Emergency Department at Hvidovre Hospital, Denmark
	Exclusion criteria: terminal illness; in treatment for a diagnosed cancer; diagnosis of chronic obstructive pulmonary disease (COPD) and participation in a COPD rehabilitation program; living outside the municipalities of Copenhagen and Broendby; inability to speak or understand Danish; inability to cooperate in tests/exercises; an expected hospitalization >24 h; assigned to physical rehabilitation in the community; a Cumulated Ambulation Score (CAS) of 0 in the sit-to-stand item
Study type	Interventional
	Allocation: randomized
	Blinding: investigator blind
Date of first enrollment	September 2013
Target sample size	80
Recruitment status	Recruiting
Primary outcome(s)	The de Morton Mobility Index
	Timeframe: change from baseline to 4 weeks after discharge (end of intervention)
Key secondary outcomes	24-h mobility measured by *activ*PAL3^TM^; isometric knee extension strength in the dominant leg; the 30-sec sit-to-stand test; habitual gait speed; hand-grip strength in dominant hand; the Barthel Index 20

### Study setting

The study will be conducted at Copenhagen University Hospital, Hvidovre, Denmark and in the participants’ own homes in the municipalities of Copenhagen, and Broendby. Hvidovre Hospital has a 552-bed capacity. Recruitment will take place in the 20-bed Emergency Department (ED) through which the majority of older medical patients (65 years or older) are admitted. There are approximately 4000 admissions of older medical patients to the ED every year, and around 50 % are discharged within the first 24 h. In Denmark, the healthcare system is public and provides feeless, tax-paid primary medical care, hospital treatment, and homecare services uniformly for all citizens.

### Study sample and recruitment procedure

Older medical patients (65 years or older) acutely admitted from their own homes to the medical services of the hospital will be included by random sampling within 24 h of admission. Each day (Monday to Friday) the primary investigator or one of three assistant investigators will receive a computer-generated list of all newly admitted older medical patients (65 years or older). The investigator will check the medical records of all the listed patients to determine their eligibility according to the inclusion and exclusion criteria as listed below:

**Inclusion criteria**Age 65 years or olderAdmitted from own home to medical services of the hospital

**Exclusion criteria**Terminal illnessIn treatment for diagnosed cancerDiagnosis of chronic obstructive pulmonary disease (COPD) and participation in a COPD rehabilitation programLiving outside the municipalities of Copenhagen and BroendbyInability to speak or understand DanishInability to cooperate in tests/exercisesTransferred to the intensive care unit or isolation-room stayAn expected hospitalization of at least 24 hAssigned to physical rehabilitation in the municipalityA Cumulated Ambulation Score (CAS) of 0 in the sit-to-stand item

Eligible patients will be visited on the ward by one of four investigators where they will be given a written description of the study to read and will be informed about the study verbally. The investigators will ensure that all questions are answered before the patient is asked to participate in the study. The Ethics Committee of the Capital Region has granted an exemption for the 24-h consent time, which is normal practice when including patients for medical research in Denmark. The exemption was granted to be able to follow the patients through their entire hospitalization and to assess their functional level before an effect of medical treatment is seen. Patients who agree to participate will be asked to sign an informed consent form to be included in the study. The patient will keep the original document and two copies will be archived.

After inclusion, baseline assessments will be performed whereafter the patients will be randomized to either: (1) intervention: progressive strength training during hospitalization and the first month after discharge (home-based), or (2) control: usual care. Shortly after discharge, four weeks (primary end point) and 6 months (follow-up) after discharge the patients will be assessed in their own homes. Figure 1 shows the study flow.

**Fig. 1 Fig1:**
[figure not shown]
Expected flow of patients

### Randomization

Patients who consent to participate will be randomly allocated to either of the two groups. Randomization will follow a computer-generated block randomization list produced by the study coordinator (JP). Randomization is stratified within the two participating municipalities. The recruitment will follow a 2:1 allocation in one of the municipalities (A) and a 1:2 allocation in the other municipality (B). This randomization procedure is followed to comply with the capacity of the municipalities (the number of physiotherapists available).

### Blinding

To ensure concealment of allocation, a study nurse will be in charge of the randomization procedure following the randomization list which will not be available to the investigators. If a patient is randomized to the intervention group, the study nurse will inform the involved physiotherapists about this allocation. Patients will be asked not to reveal to the investigators to which group they belong. The discharge test in the patient’s home will be conducted before the first post-discharge training session to avoid the investigator seeing the exercise equipment in the home. Moreover, 4-week follow-up assessments will take place between 4 and 5 weeks after discharge, and the study nurse will inform the investigators when patients are ready for the 4-week follow-up assessment (end of intervention) regardless of allocation, to avoid the investigators guessing who belongs to which group. Also, all training equipment will be removed from the patients’ homes before the 4-week assessment to ensure that the investigators do not see the equipment in those homes. Additionally, all contacts with physiotherapists in the hospital and in the municipalities regarding allocation, questions about the protocol and other practicalities will be undertaken by the study nurse to ensure blinding of the investigators. In the case of a possible adverse event and the unavailability of one of the co-authors to evaluate the severity of the event, the allocation of the patient can be revealed to the investigators in order to assure proper treatment of the patient. If the patient can no longer participate in assessments he/she will be excluded from the study. Otherwise, the patient will remain in the study and all information of all such events will be reported in the manuscript.

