### Primary outcome measure

The primary outcome will be change in the DEMMI score from baseline to 4 weeks after discharge (end of intervention, primary end point). The DEMMI is a valid and reliable measure of mobility in both acute and subacute older medical patients and in community-dwelling older adults [62, 72–74], and can be used to accurately monitor mobility in older adults [72]. It includes observations ranging from mobility to dynamic balance and is scored on a scale from 0 to 100 with 100 representing the highest level of mobility [72, 73], and with a minimal clinically important difference of 10 points for acute older medical patients [72].

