### Data collection

The primary investigator and a team of three assistant investigators will perform all baseline and follow-up assessments. All four investigators are trained physiotherapists with 1 to 15 years of experience.

The admission assessments will be performed on the acute medical admissions ward or on an internal medicine ward at Copenhagen University Hospital, Hvidovre, Denmark, within the first 48 h after admission. All follow-up assessments will be performed in the patient’s own home, and the same investigator will assess the same patient at all assessments whenever logistically possible, to promote patient retention.

During each training session the supervising physiotherapist will complete an exercise diary consisting of information about the level of exercise attained according to the progression models, the extra load added (kg), and the number of sets and repetitions performed at each level. Self-reported pain will be registered immediately before and after each training session by the use of the VRS. Moreover, the physiotherapist will register reasons for non-participation as well as the amount of protein consumed after each training session. The patient time line including data collection is presented in Table 3.

**Table 3 Tab3:** Patient timeline

	Study period						
Time point	Admission	Baseline	Hospital intervention	Discharge assessment	Home intervention	4-week assessment	6-month assessment
		≤48 h after admission	Daily during hospitalization	In patient’s home	3 times per week for 4 weeks in patient’s home	In patient’s home	In patient’s home
Enrollment							
Eligibility screen	X						
Informed consent	X						
Study groups							
Strength training		X	X	X	X	X	X
Control		X		X		X	X
Assessments							
Baseline assessment^a^		X					
Primary outcomes		X		X		X	X
Secondary outcomes		X		X		X	X
Descriptive variables and possible confounders and modifiers		X		X		X	X

^a^See Table 2 for a detailed description of assessed variables

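### An investigator told the allocation under the adverse-event fallback may go on to rate that patient's DEMMI, because the same-assessor rule makes no exception for loss of blinding

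*Protocol article*

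**What the plan says.** Four statements in the protocol article bear on this point.

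- **Blinding, the trigger.** The fallback has two conditions: "In the case of a possible adverse event and the unavailability of one of the co-authors to evaluate the severity of the event". When both are met, "the allocation of the patient can be revealed to the investigators", for the sake of the patient's care.
- **Blinding, what follows.** A patient who can no longer take part in assessments is excluded. For everyone else: "Otherwise, the patient will remain in the study and all information of all such events will be reported in the manuscript".
- **Data collection.** The investigators are the outcome assessors: "The primary investigator and a team of three assistant investigators will perform all baseline and follow-up assessments". They are also tied to individual patients: "the same investigator will assess the same patient at all assessments whenever logistically possible, to promote patient retention".
- **Primary outcome measure.** "The primary outcome will be change in the DEMMI score from baseline to 4 weeks after discharge". The same section describes DEMMI as built from observations and scored from 0 to 100.

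Study design describes the trial as investigator-blinded.

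**The concern.** Patients and treating physiotherapists know the allocation, so blinding of the assessors is the main protection for a primary outcome scored by observation. The Blinding section guards it carefully elsewhere. The discharge test comes before home training starts, equipment is removed before the 4-week visit, and the study nurse calls the 4-week visit regardless of allocation and handles contact with the physiotherapists. The adverse-event fallback is the one place where the plan itself opens the blind to the assessors. It does not say who rates the patient afterwards, and the only stated rule on who rates is the continuity rule.

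At stake is a rating made with knowledge of the allocation. If such ratings were shifted in one direction and fell mostly in one arm, they would bias the estimated difference in DEMMI change.

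**Working it through.** **Step 1: read the rules together.**

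| Question | Answer in the article | Section |
|---|---|---|
| Who may learn the allocation? | The investigators (plural), as a fallback | Blinding |
| Does the patient stay in? | Yes, if still assessable | Blinding |
| Who does the assessments? | The same four investigators | Data collection |
| Who sees this patient next? | The same investigator, subject only to logistics | Data collection |
| What is rated? | DEMMI, from observation | Primary outcome measure |

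Following each rule as written can put an unblinded investigator on the 4-week DEMMI. Nothing stated limits the disclosure to one investigator or passes the patient to a blinded colleague.

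**Step 2: reproduce the plan's own figure, for scale.** Inputs from Sample size: target difference 10 points, SD of change 12.8, two-sided 5 % level, 80 % power.

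- Standardised difference: 10 / 12.8 = 0.78.
- The two-sample t test needs 26.7, hence 27 per arm, with power 80.4 % at 27. This agrees with the stated 27.
- Standard error of the difference: 12.8 × √(2/27) = 3.48 points.

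**Step 3: size of the bias.** If k of the 27 patients in one arm are rated by an unblinded assessor and each score is shifted by b points, the between-group difference shifts by k × b / 27. The article gives neither k nor b, so both are assumed. The type I error is the two-sided normal approximation, Φ(−1.96 + s) + Φ(−1.96 − s), with s = shift / 3.48.

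| k | b | Shift (points) | Shift / SE | Type I error |
|---|---|---|---|---|
| 1 | 5 | 1 × 5 / 27 = 0.19 | 0.05 | 5.0 % |
| 2 | 5 | 2 × 5 / 27 = 0.37 | 0.11 | 5.1 % |
| 2 | 10 | 2 × 10 / 27 = 0.74 | 0.21 | 5.5 % |
| 4 | 10 | 4 × 10 / 27 = 1.48 | 0.43 | 7.1 % |

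With k = 0 there is no effect. The last row is a severe case, since b = 10 means each affected rating is off by the whole minimal clinically important difference. The table also assumes that all affected patients are in one arm and shifted the same way. Unblinding in both arms, or shifts in mixed directions, would give less.

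**The case against.** The strongest reply is that the unblinding route is narrow and the article is a condensed document. Evaluation by a co-author is the default, and Data monitoring adds a geriatrician hotline as another source of advice. Patients who can no longer be assessed leave the study, and events after the 4-week visit cannot touch the primary endpoint. Data monitoring also says that the study will be stopped if an adverse event is attributed to training or testing, which further limits how many later ratings could be affected. A rule for reassigning a patient after a rare event might stand in the full protocol, which is not shown. The Blinding section already promises to report all such events.

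Most of this stands as an argument about size: the number of affected patients may well be zero or one. It does not remove the point. The article states both the disclosure rule and the continuity rule, and it is their combination, not a missing detail, that permits an unblinded rating. The promise to report events does not keep the rater blinded.

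Three stronger readings are tempting but not supported.

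- A reader might infer that the plan instructs the unblinded assessor to continue. It does not. The continuity rule is general, is there for retention, and does not mention unblinding.
- A reader might infer that three blinded assessors are always left. The wording is plural and does not say that only one investigator is told.
- A reader might infer that unblinding must fall mainly in the intervention arm, because physiotherapists see those patients often and report events. That is plausible, but investigators report events too and see both arms, and the article gives no event rates by arm.

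**Conclusion.** The point holds as a small gap in the protection of the blind. Under a fallback with two conditions, the stated rules allow an investigator who knows the allocation to rate the observation-based primary outcome at 4 weeks. With assumed values of 1 to 4 of 27 patients in one arm and a shift of 5 to 10 points each, the bias is about 0.2 to 1.5 points, against a standard error of about 3.5 and a target difference of 10. At the low end, the type I error is essentially unchanged; at the severe end, it is about 7 %. Neither the direction nor the arm of any bias is established by the article. The change is worth making because it is cheap, not because the primary result is likely to turn on it.

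**What to change.** - **Blinding:** state that a fallback disclosure goes only to the one investigator who needs it.
- **Data collection:** add an exception to the continuity rule, so that a still-blinded member of the existing team of four does all remaining assessments of that patient.
- **Reporting:** give the number of unblinded patients by arm, alongside the event reporting already promised.

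The cost is a scheduling rule and a change of rater for a few patients, with some added between-rater variation and some loss of the continuity meant to help retention. Recruitment was still open when the article was submitted, so the rule could apply to patients not yet assessed at 4 weeks.

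A sensitivity analysis that leaves out visits rated by an unblinded assessor is not recommended. It would remove patients selected by adverse events and, with so few of them, would settle little. When and why allocation is revealed for a patient's care needs no change on this account.

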### Sample size

Based on data from an unpublished cohort study performed at Hvidovre Hospital, 25 consecutively included older medical patients had a mean change in the de Morton Mobility Index (DEMMI) [62] score of 1.8 and a standard deviation of 12.8 from admission to 1 month after discharge. A change of 10 points in the DEMMI score is considered a minimal clinically important difference in acute older medical patients [62]. To be able to detect a 10-point difference in the between-group change in the DEMMI score at the 4-week assessment (primary end point), we will need a sample size of 27 patients per study arm to obtain a type I error rate of 5 % and a power of 80 % for a two-sample *t* test of a normal mean difference with a two-sided significance level. We will continue to recruit patients until 54 patients have been assessed for the primary end point (4 weeks). In case of a skewed distribution of patients in the two groups (intervention and control), we will recruit until both groups contain 25 patients. We expect a maximum of 80 patients to be included in the study.

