### Primary analysis for the primary outcome

A mixed-model analysis (dif (discharge-baseline), dif (4 weeks-baseline), dif (6 months-baseline)) will be performed using the SAS procedure PROC MIXED. The patient identification number and municipalities will be modeled as random variables, and both group and time will be modeled as fixed factors. The between-group difference in change in DEMMI will be estimated from the interaction between the time and group variable. The primary outcome will be the between-group difference in change in the DEMMI score from baseline to 4 weeks after discharge (end of intervention). The primary analysis will follow the intention-to-treat principle using multiple imputation in case of missing outcome measures and will be unadjusted.

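### The rule that a patient who can no longer be assessed is excluded from the study conflicts, read literally, with the intention-to-treat primary analysis; the direction of any bias is unknown

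*Protocol article*

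**What the plan says.** The Blinding section of the protocol article sets out when allocation may be revealed to the investigators: "In the case of a possible adverse event and the unavailability of one of the co-authors to evaluate the severity of the event". Directly after this comes the rule at issue: "If the patient can no longer participate in assessments he/she will be excluded from the study". The alternative follows: "Otherwise, the patient will remain in the study and all information of all such events will be reported in the manuscript". No arm is named, and nothing says whether exclusion means the end of follow-up or removal from the analysis.

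The section on the primary analysis of the primary outcome says: "The primary analysis will follow the intention-to-treat principle using multiple imputation in case of missing outcome measures and will be unadjusted". The model is a repeated-measures model on changes from baseline: "A mixed-model analysis (dif (discharge-baseline), dif (4 weeks-baseline), dif (6 months-baseline)) will be performed using the SAS procedure PROC MIXED". A discharge value therefore enters the model in its own right.

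The Sample size section bases recruitment on patients assessed at 4 weeks: 54 in total, with at most 80 expected to be included.

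**The concern.** A patient who is randomized, has an adverse event and can then no longer do the assessments has a missing outcome. The primary analysis says how such a patient is handled: kept in the randomized arm, with the outcome imputed. The Blinding section says that the patient is excluded from the study. Anyone building the analysis set from the second rule would drop a patient whom the first rule retains.

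The loss would not be random. The outcome is mobility, and inability to take part in assessments after an adverse event is plausibly linked to poor mobility. The rule also stands next to the provision for revealing allocation, and the article does not say who decides that a patient can no longer take part. That decision could therefore be made with the arm known.

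At stake are the comparability of the randomized groups and data already in hand. A patient excluded after the discharge visit would lose an observed discharge change. One excluded between the 4-week and 6-month visits would lose even an observed primary outcome.

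**Working it through.** **The two rules side by side.** Take a randomized patient with a baseline and a discharge DEMMI score, then an adverse event, then no further assessment.

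- Under the primary-analysis section, the patient is in the intention-to-treat set, the discharge change is used, and the 4-week and 6-month changes are imputed.
- Under the Blinding section read literally, the patient is not in the study. Neither the discharge change nor an imputed 4-week change contributes.

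The two agree only if exclusion means that assessments stop. The article does not say so, and the next sentence contrasts exclusion with remaining in the study, not with continuing assessments.

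**The plan's own scale.** Inputs from the Sample size section: difference 10 points, standard deviation of change 12.8, two-sided 5%, power 80%.

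- Normal approximation: n = 2 × (1.96 + 0.842)² × 12.8² / 10² = 25.7, so 26 per arm.
- Two-sample t test: 26.7, so 27 per arm, with power 80.4% at 27. This reproduces the stated 27.
- Standard error of the difference at 27 per arm: 12.8 × √(2/27) = 3.5 points.

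**Bias from literal exclusion.** Let f be the share of an arm that is excluded and D the amount by which the mean change of the excluded patients is worse than that of the retained patients. The mean of the whole arm is the retained mean minus f × D, so dropping the excluded patients raises the arm mean by f × D. For the between-group difference (training minus control):

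bias = f_T × D_T − f_C × D_C, which is (f_T − f_C) × D when the deficit is the same in both arms.

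The documents give neither f nor D. The values below are assumptions, chosen to show the range with a common D:

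| Excluded, training vs control | D = 10 | D = 20 | D = 30 |
|---|---|---|---|
| 10% vs 0% | +1.0 | +2.0 | +3.0 |
| 10% vs 5% | +0.5 | +1.0 | +1.5 |
| 10% vs 10% | 0 | 0 | 0 |
| 5% vs 10% | −0.5 | −1.0 | −1.5 |

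A positive sign favours training. Equal shares with unequal deficits also leave a bias: 10% in each arm with deficits of 30 and 10 gives 0.10 × 30 − 0.10 × 10 = +2.0, and −2.0 if the deficits are swapped.

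**The case against.** The strongest defence is that the sentence stands in a section on blinding and mentions no analysis set. Excluded from the study may mean only that study visits end. The statistical section then governs, and the patient is an ordinary case of a missing outcome. This reading is possible and would make the passages compatible, so the contradiction is not certain. But it is stated nowhere, and the contrast with remaining in the study points the other way. The ambiguity stands either way.

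Three stronger inferences are tempting, and the article supports none of them.

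- *That the rule favours training.* A reader might argue that events caused by training arise only in the training arm. The rule covers both arms, however, and acutely admitted older patients can deteriorate for reasons unrelated to training. The Data monitoring section provides for stopping the study if an event is judged to be caused by training or testing, so recognised training events fall under a different rule. More frequent contact in the training arm might bring more events to notice there, but no rates are given.
- *That about a third of patients fall under it.* The gap between 80 included and 54 assessed is 26/80 = 32.5%. That is a ceiling for missing 4-week assessments from any cause, including refusal, death and loss to follow-up. It is not a rate of exclusion after adverse events.
- *That harm is hidden.* The Blinding section commits to reporting all such events in the manuscript. That sentence opens with the alternative case, but its scope reads naturally as covering these events, and the article also commits to CONSORT reporting.

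**Conclusion.** The point holds as a conflict in the stated rules. Read literally, the Blinding section prescribes an outcome-related exclusion after randomization that cannot be squared with the intention-to-treat analysis with multiple imputation, and that would discard DEMMI values the primary model uses. Both rules are in the article, so this is not a detail left to a separate analysis plan.

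The direction and size of any bias are unknown. The range of −1.5 to +3.0 points in the table rests wholly on assumed shares and a common deficit. It compares with a target difference of 10 points and a standard error of about 3.5. It shows that the handling of these patients could matter, not that it will. With equal shares and equal deficits the bias is zero. The remedy is cheap and should be made before the data are analysed.

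**What to change.** Replace the exclusion sentence in the Blinding section with wording such as:

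> A patient who can no longer be assessed stops assessments but remains in the analysis as randomized; all data already collected are kept, and missing DEMMI values are handled by the multiple imputation planned for the primary analysis.

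The cost is one sentence. It changes neither clinical management nor the sample size. The Study status section says that recruitment is ongoing, so the wording can be settled before analysis.

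This restores the randomized analysis set. It does not by itself remove all bias, because imputation under missing at random recovers only what the observed data predict. A sensitivity analysis for data missing not at random, limited to patients who are unassessable because of deterioration, would be a useful optional addition at the cost of one extra run. Its absence from the article is not a fault.
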